In the experimental arm, bursts of three pulses at 100 Hz are phase-locked to the trough of the ongoing theta oscillation (4–8 Hz), ensuring synchronization with intrinsic brain rhythms. Circles highlight stimulation timing relative to the oscillatory phase. Of note, in the experimental condition, stimulation is not delivered on every detected theta trough but occurs with a mean inter-burst interval of approximately 3.5 s, corresponding to every 15th–20th theta cycle. In the control arm, bursts of three pulses at 50 Hz are delivered in a fixed 5 Hz pattern independent of the EEG signal (open-loop). Hereby each session in the control condition consists of 600 pulses applied in 2 s “on” / 8 s “off” cycles.

In both interventions, 600 TMS pulses will be delivered per session corresponding to 12.000 TMS pulses during the entire 4 weeks of TMS therapy. Stimulation intensity will be set to 120% resting motor threshold (RMT) or the highest tolerated intensity if this is below 120% RMT. If required, a ramp-up period will be used for a maximum of the first three sessions to accommodate patients that don’t immediately tolerate the desired stimulation intensity. Stereoscopic neuronavigation (Localite GmbH, Bonn, Germany) based on individual anatomical MRI data will be used to position the coil, where DMPFC and DLPFC target locations will be pre-determined based on the individual MRI data and identifying the respective target gyrus using standard anatomical methods [42].

To ensure blinding of the patients, all setup components are implemented identically in both conditions, that is, a surface EEG is recorded through a 5-channel equipment during the TMS intervention in both the experimental and in the standard condition. But only in the experimental condition is the EEG used to trigger the TMS pulses; in the control condition, the EEG is recorded but not considered for triggering the TMS pulse. To ensure double-blinding, the rater is blinded as well, as the rater must not be present during the intervention procedure and does not have access to non-rater-related documentation.

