### Criteria for discontinuing or modifying allocated interventions

If the stimulation is not tolerated by the patient, the stimulus intensity will be first adjusted to the highest tolerated intensity and then gradually adjusted to the required intensity over max. 3 sessions. If the patient cannot become acquainted with the treatment conditions (e.g., stimulus intensity) within three sessions, additional participation is not feasible. Withdrawal from the study is also required if the subject misses more than 4 planned treatment sessions. In the case of up to 4 missed planned treatment sessions, the missed sessions will be offered at the end of the intervention period, so that each enrolled patient will receive 20 sessions. However, we strive to keep the number of treatment cancellations and postponements to a minimum. Patients who withdraw from the study will be included in the primary statistical analysis (cf. section “Statistical Methods”).

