Also, influential factors such as tolerability of the stimulation within the different treatment conditions can be relevant for clinical feasibility and the overall treatment outcome, thus such aspects will be considered with respect to the treatment arm. We expect that rTMS treatment over the DMPFC will be more comfortable than over DLPFC due to the more medial prefrontal target, yet a longer duration of the treatment needs to be endured (15–20 min). TBS over DLPFC might be more uncomfortable than TBS over DMPFC due to the more laterally located target area closer to the temporalis muscle, which might twitch under stimulation. Yet the treatment duration is shorter (3 min). Tolerability and related complaints of the patients, as well as the reasons for drop out of patients will be documented in the CRFs. Sex and gender may influence responsiveness to rTMS, although evidence is mixed. Some studies have suggested higher response rates in women [61, 62], potentially linked to hormonal influences or anatomical factors such as scalp-to-cortex distance, while others have not found significant sex-related differences in clinical outcomes [63]. Given the limited sample size of this pilot trial, we are not powered to formally test gender-specific effects. Nevertheless, we will document and report the gender distribution of participants and conduct exploratory analyses of treatment response by gender. Regarding inter-individual anatomical variability in terms of responsiveness to TMS, in the present protocol the stimulation intensity is defined relative to the resting motor threshold without correction for e.g. scalp-to-cortex distance as we prioritized adherence to the established FDA-approved iTBS standard protocol. Nevertheless, all participants undergo structural MRI, which will enable exploratory analyses of how anatomical factors may relate to treatment outcome. In a subsequent confirmatory trial, we plan to incorporate scalp-to-cortex distance correction or electric-field modeling to improve individual dose standardization.

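### Two sections of the protocol article give opposite outcomes for a patient who still tolerates only less than 120% RMT after the ramp-up

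*Protocol article*

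**What the plan says.** All references are to the protocol article.

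- **Intervention description:** "Stimulation intensity will be set to 120% resting motor threshold (RMT) or the highest tolerated intensity if this is below 120% RMT". No minimum and no time limit are attached to the lower setting. Ramp-up follows as a separate provision: "If required, a ramp-up period will be used for a maximum of the first three sessions".
- **Criteria for discontinuing or modifying allocated interventions:** when stimulation is not tolerated, "the stimulus intensity will be first adjusted to the highest tolerated intensity and then gradually adjusted to the required intensity over max. 3 sessions". Then: "If the patient cannot become acquainted with the treatment conditions (e.g., stimulus intensity) within three sessions, additional participation is not feasible". The next sentence gives too many missed sessions as a ground on which withdrawal is also required. The section adds that withdrawn patients stay in the primary analysis.
- **Discussion:** "We expect that rTMS treatment over the DMPFC will be more comfortable than over DLPFC due to the more medial prefrontal target", and "TBS over DLPFC might be more uncomfortable than TBS over DMPFC due to the more laterally located target area closer to the temporalis muscle". The same paragraph says that the experimental session is longer and has to be endured, and that tolerability will be considered by treatment arm.
- **Statistical methods:** the analysis is by intention to treat. Missing values are multiply imputed with the percentage of sessions as a covariate. Zero change, complete case and last observation carried forward are sensitivity analyses. A per-protocol analysis is added if that set differs from the intention-to-treat set by more than four patients.

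**The concern.** The article states two rules for the same patient. One accepts a tolerated intensity below 120% RMT as the intensity at which the patient is treated. The other makes that intensity a temporary step and ends participation if the required level is not managed in time. The required level is not defined where it is used.

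This is the tolerability-based exit from treatment in a trial planned around 14 assessable patients per arm, and recruitment is already under way. If the rule is not fixed, who stays on treatment depends on which section is followed. The arms use different targets with different expected discomfort, so an unfixed exit rule also weakens the tolerability comparison that the Discussion announces. Few withdrawals for intolerance could mean good tolerability, or simply that patients were kept at a reduced intensity.

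**Working it through.** **1. The two rules side by side.** Take a patient who, after session 3, tolerates at most some intensity below 120% RMT.

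| Question | Intervention description | Discontinuation criteria |
|---|---|---|
| Status of the highest tolerated intensity | The set intensity, if below 120% RMT | First step only |
| Time limit on it | None stated | At most three sessions to reach the required intensity |
| Outcome for this patient | Continues | Further participation not feasible |
| Sessions received | Up to 20 | About 3, i.e. 3/20 = 15% |
| Pulses received, at 600 per session | Up to 12,000 | About 3 × 600 = 1,800 |

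Continuation up to session 20 is inferred from the absence of a time limit; it is not stated.

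**2. Can one reading satisfy both?** Suppose the required intensity already means 120% RMT or the highest tolerated level. Then "first adjusted to the highest tolerated intensity and then gradually adjusted to the required intensity over max. 3 sessions" would describe moving from the highest tolerated intensity to the same intensity. The sentence names two successive levels, so this reading is strained.

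**3. Where the choice enters the analysis.** Withdrawal does not remove the patient from the primary analysis. It changes:
- the exposure behind any outcome that is observed;
- the sessions covariate in the imputation (about 15% instead of up to 100%), if the outcome is missing;
- the zero-change, last-observation and complete-case results;
- the per-protocol set and, through the more-than-four-patients trigger, possibly whether that analysis is run (assuming early withdrawals leave the set).

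**4. Planning figures.** From Sample size: improvement of 48% (control) and 68% (experimental), SD 17.9, difference 20 points. The standardised difference is 20/17.9 = 1.117. A two-sided t-test at α = 0.05 and 80% power needs 13.605 per group (noncentral t), which reproduces the stated 13.6. With 14 per group, power is 0.812. The 34 to be randomised give 17 per arm.

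**5. Illustration of size and sign.** The documents give no rate of patients who tolerate only less than 120% RMT, so the rates below are assumptions. Suppose the discontinuation criteria are followed and each withdrawn patient is scored as zero change, which is one of the listed sensitivity analyses. With withdrawal proportions p_C (control) and p_E (experimental), the expected difference is 68(1 − p_E) − 48(1 − p_C).

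| p_C / p_E | Withdrawn of 17 (control / experimental) | Expected difference | Shift from 20 |
|---|---|---|---|
| 5% / 5% | 0.85 / 0.85 | 64.6 − 45.6 = 19.0 | −1.0 |
| 10% / 5% | 1.7 / 0.85 | 64.6 − 43.2 = 21.4 | +1.4 |
| 20% / 5% | 3.4 / 0.85 | 64.6 − 38.4 = 26.2 | +6.2 |
| 30% / 10% | 5.1 / 1.7 | 61.2 − 33.6 = 27.6 | +7.6 |
| 5% / 10% | 0.85 / 1.7 | 61.2 − 45.6 = 15.6 | −4.4 |
| 5% / 20% | 0.85 / 3.4 | 54.4 − 45.6 = 8.8 | −11.2 |

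Under the Intervention description none of these patients is withdrawn. The difference then stays at 20, provided reduced intensity does not lower the response, which is a further assumption. The table concerns one sensitivity analysis only. It shows that the sign follows the assumed rates.

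**The case against.** The best defence is that the discontinuation criteria never mention 120% RMT, and that the only definition of the set intensity is in the Intervention description. The exit clause could then be meant for a patient who cannot tolerate treatment at all, not for one who is comfortable at a reduced setting. That may be what was intended, but the text does not say it, and the two-step wording works against it. What stands is that a clarification may be all that is needed.

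A reader might go further than the documents allow in four ways.

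- **That early stopping will fall mainly on the control arm and favour the experimental one.** The expectation of more discomfort at the control target is hedged, and the same paragraph sets the longer experimental session against it. The exit clause refers to treatment conditions generally, with intensity only as an example, so session length could count too.
- **That the unblinded therapy provider decides who is withdrawn.** Blinding says only that this person cannot be blinded. For adverse events, Therapy visit has a study physician consulted and gives the principal investigator the decision on further participation.
- **That the choice would go unrecorded.** A structured self-report follows each session, tolerability complaints and reasons for drop-out go into the case report forms, and Provisions for post-trial care continues follow-up unless the patient withdraws consent for it.
- **That the primary contrast shifts by a known amount.** With 14 per arm and an assumed 10% improvement in a stopped control patient, each such patient lowers the control mean by (48 − 10)/14 = 2.7 points, and four lower it by 10.9. The 10% has no source, a patient at reduced intensity is credited with the full 48%, every stop is placed in one arm, and the planned imputation is ignored. This is not an estimate for this trial.

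**Conclusion.** The contradiction stands as a matter of text. For a patient who remains below 120% RMT after the ramp-up, one section permits continued treatment and the other ends participation, and the term that would decide between them is undefined. For that patient the difference is up to 20 sessions against about 3.

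The effect on the trial cannot be sized, because no rate of such patients is given. In the illustration, the zero-change sensitivity analysis moves by −11.2 to +7.6 points against the planned 20, depending wholly on assumed withdrawal rates. Neither direction is established, and the figures do not describe the primary analysis, which keeps withdrawn patients and imputes missing outcomes.

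This should be fixed: it determines who leaves treatment in a small trial that is already recruiting. It does not invalidate the design or show bias towards either arm.

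**What to change.** 1. Reconcile the Intervention description and the discontinuation criteria into one rule for a patient who has not reached 120% RMT by the end of the ramp-up. Define required intensity and apply the rule identically in both arms. Which rule it is, is for the investigators to decide.
2. State that ending stimulation for intolerance ends treatment only. The T10, T20 and P2 assessments then continue, as Provisions for post-trial care already allows, unless consent for follow-up is withdrawn. Because Assessment visits ties these time points to sessions, give them calendar times for a patient who has stopped.
3. Tabulate delivered %RMT by arm next to the withdrawals for intolerance, so that tolerability can be read whichever rule is chosen.

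The cost is protocol wording and, if the case report form does not already hold delivered intensity per session, one field. No extra patients, visits or staff are needed. Patients already treated should be described by what was actually done.

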### Measurement procedures

MRI

The MRI images will be acquired at a Siemens 3 Tesla MRI scanner in the MRI Research Center of Tübingen (Department Biomedical Magnetic Resonance, [name]. phil. nat. Dipl.-Phys. [name], [name]). Patients are placed in the scanner with earplugs and an emergency ball. Visual and verbal contact to the patients is maintained from the control room. No drugs or contrast agents are used during MRI examinations.

Study participants are evaluated by a medical doctor for MRI contraindications and need to give written informed consent before the scan. Subjects are required to give written consent that if the scan reveals a gross anatomical abnormality, they will be informed and need to take further diagnostic work-up outside of the study. Acquired scans are performed for scientific reasons with parameters optimized according to the requirement of the stimulation and thus do not provide sufficient diagnostic value in case of structural abnormalities.rTMS

Study participants will be seated on a comfortable reclining chair with both arms relaxed. A high-frequency capable TMS stimulator (MagPro XP, MagVenture, Denmark) with a figure-of-eight coil (Cool-B65, inner coil winding diameter 35 mm) and a TMS-compatible EEG setup (ActiCHamp, BrainProducts, Gilching, Germany) will be used. For DMPFC-EEG-TBS, TMS pulses will be triggered from a custom real-time digital biosignal processing system based on the ongoing oscillatory theta brain activity in the left DMPFC as recorded by surface EEG.Stereoscopic Neuronavigation

Stereoscopic neuronavigation (Localite GmbH, Bonn, Germany) will be used to track the position of the coil relative to the head and to determine the appropriate stimulation sites (DMPFC and DLPFC, respectively).EEG

EEG recordings will be carried out using a TMS-compatible, optically isolated amplifier (ActiCHamp, BrainProducts, Gilching, Germany).

For the theta screening and the pre- and post-assessment surface EEG series will be recorded for 5 min with eyes open using a TMS-compatible 32-channel gel filled sintered ring electrode EEG cap (ActiCap, BrainProducts, Gilching, Germany) using the same optically isolated amplifier as described above. Electrode impedances are kept below 10 kΩ, the sampling rate is set to 1,000 Hz with 24-bit resolution, and FCz serves as the reference electrode. The primary purpose of the screening EEG procedure is to evaluate the presence of a detectable theta rhythm in the 4–8 Hz frequency range over midline frontal electrodes. Spectral power is computed in real time, and a graphical representation of the frequency spectrum is generated for visual inspection. A clearly identifiable theta peak is required for study inclusion, as the EEG-synchronized stimulation depends on reilable phase detection in this frequency band. This screening step ensures the technical feasibility of the intervention and serves as an additional eligibility criterion. In addition to the screening EEG, resting-state EEG is also recorded immediately before the start of treatment (pre-assessment) and after the final stimulation session (post-assessment). The purpose of these recordings is to evaluate changes in spectral power and functional connectivity across treatment, with a focus on the theta frequency band. Exploratory analyses will also investigate alterations in other frequency ranges and potential shifts in frontal network dynamics.

For the stimulation sessions, a five-channel setup is employed with an AFF1h-centered Hjorth montage (AFF1h, AFF2h, AFp1, FFC1h, AFF5h) to capture frontal theta oscillations over the left dorsomedial prefrontal cortex (DMPFC) {Gordon, 2021 #12}. EEG is recorded with the identical montage and equipment in both conditions as described above, but is not used to control the timing of stimulation in the control condition, thereby maintaining blinding while also enabling exploratory offline analyses.Real-time EEG algorithm

The real-time pipeline consists of a band-pass filter in the theta range (4–8 Hz), a 50 Hz notch filter to remove line noise, and continuous monitoring for artifacts. Theta oscillations are extracted from the AFF1h channel, and instantaneous phase is computed using a Hilbert transform with latency compensation. TMS bursts are triggered at the trough of the theta cycle, with prediction to compensate the fixed delay of 15–20 ms arising from amplifier buffering, signal processing, and stimulator triggering; the predictor advances the command by ~ 30–45° at 6 Hz [30]. To allow undisturbed phase estimation, a hard refractory period of 1.0 s is imposed after each burst. Thereafter, the next eligible trough is used, selecting every 15-20^th^ trough to obtain a mean interburst interval ~ 3.5 s. Session level phase-locking metrics are computed online to verify timing accuracy (see also Fig. 2). This calibration procedure follows established practice in phase-specific TMS research [30] and recent delay analyses highlighting uncompensated transport latency as a critical determinant of phase-locking accuracy [43]EMG/MEP

Surface electromyography (EMG) will be obtained through an optically isolated battery powered biosignal amplifier (ActiCHamp, BrainProducts, Gilching, Germany) using bipolar electrodes from right hand muscles (first dorsal interosseous and abductor pollicis brevis muscles). This enables determining the RMT, which is needed to individualize stimulation intensities during the rTMS protocols. RMT is defined as the minimum stimulus intensity needed to evoke motor evoked potentials (MEP) of > 50 µV peak-to-peak amplitude in the target muscle in at least 5 out of 10 consecutive trials using a figure-of-eight TMS coil oriented 45° away from the midline over the hand representation of left primary motor cortex [44]. Patients will be requested to relax and stay awake during the experiments.Clinical Assessments

Clinical assessments regarding the severity of the depression before and after the TMS treatment will be performed by a blinded rater using the MADRS and HDRS-17 scales.Self-Report

Subjects will be asked to complete the Beck-Depressions-Inventory-II (BDI-II) (this will take 5 min) and the Inventory of depressive symptoms-30 (IDS-30) (this will take 10 min) at baseline (pre-assessment), after the 10th session (intermediate assessment), after the last session (post-assessment) and at the follow-up visit four weeks after the last intervention (follow-up assessment). Following each intervention session, a structured self-report will be documented, to assess whether any side-effects occurred from the stimulation. Side effects will be documented on a separate adverse event sheet.

### Criteria for discontinuing or modifying allocated interventions

If the stimulation is not tolerated by the patient, the stimulus intensity will be first adjusted to the highest tolerated intensity and then gradually adjusted to the required intensity over max. 3 sessions. If the patient cannot become acquainted with the treatment conditions (e.g., stimulus intensity) within three sessions, additional participation is not feasible. Withdrawal from the study is also required if the subject misses more than 4 planned treatment sessions. In the case of up to 4 missed planned treatment sessions, the missed sessions will be offered at the end of the intervention period, so that each enrolled patient will receive 20 sessions. However, we strive to keep the number of treatment cancellations and postponements to a minimum. Patients who withdraw from the study will be included in the primary statistical analysis (cf. section “Statistical Methods”).

### Strategies to improve adherence to interventions

Adherence to the intervention is considered to be high as patients decide to participate in this brain stimulation study on their own initiative. TMS treatment is non-invasive, painless and is generally considered to be well tolerated. Participation adherence is expected to be also increased by the ramp-up method with a familiarization phase to the stimulation intensity (if required) and the possibility of 4 missed planned treatment appointments.

### Relevant concomitant care permitted or prohibited during the trial

No specific antidepressant medication is mandatory. However, if present, the antidepressant therapy must be kept constant, which means that medication at or above the “minimum oral dose” (MOD) specified in the Antidepressant Treatment History Form: Short-Form (ATHF-SF) [45] has to remain unchanged 4 weeks before and 6 weeks during study treatment. Changes below the MOD are considered as uncritical. Changes after the end of treatment are registered in the follow-up sessions. Critical changes during the treatment period lead to exclusion from the per protocol analysis.

Patients are advised not to undergo any concomitant therapies if possible. In the case of ongoing therapies (e.g., psychotherapy), patients are asked to keep these constant in intensity and frequency throughout the study period.

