### Eligibility criteria

Subject inclusion criteria.Subjects are between 18 to 65 years oldSubjects meet DSM-5 criteria for current major depressive disorder (MDD), confirmed with the Structured Clinical Interview for DSM-5.Subjects score 20 points or more on the Montgomery–Åsberg Depression Rating Scale (MADRS).Subjects must have had at least one non-response in accordance with the Antidepressant Treatment History Form (ATHF), meaning a failure to achieve remission in a previous pharmacological antidepressant treatment trial of sufficient dosage and duration, meaning a dose considered to be effective (e.g., superior to placebo in controlled clinical trials) and a duration needed to be sufficient to produce a robust therapeutic effect (e.g., 4–6 weeks); this treatment failure can apply for the current or any prior depressive episode. Demonstration of medication resistance for the current episode is not required, if resistance occurred during any prior depressive episode.Subjects must exhibit a sufficiently detectable frontal-midline theta rhythm during the EEG screening procedure. This is assessed with a 32-channel resting-state EEG (5 min, eyes open) conducted at the screening visit. Theta power spectra are computed and visually inspected for the presence of a clear peak in the 4–8 Hz range over midline frontal electrodes. Only patients with a discernible theta peak are eligible, as this is required to ensure feasibility of the real-time algorithm.Subject is in otherwise good physical and mental health. Subject understands the study procedures and agrees to participate in the study by giving written informed consent.Subject is willing to comply with the study restrictions (cf. “paragraph relevant concomitant care …”)If antidepressant medication is being taken, it has to be taken for at least 2 weeks before inclusion in the study and the dose or active substance must not have been changed. It is necessary that no change in medication will be made until the end of the study (last visit takes place 4 weeks after the last therapy session). If a change in medication is necessary, further study participation is not possible.

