### Participant timeline

The TMS intervention duration for each subject is 4 weeks (20 sessions, 5 sessions per week). The maximum study duration including screening, MRI scan, TMS intervention and a 4-weeks follow-up measurement for each subject will be 3 months. The time course of events can be seen in Table 1.

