#### Therapy visit

A 5-channel EEG cap with an AFF1h-centered Hjorth montage (AFF1h AFp1, AFF2h, FFC1h, AFF5h) with active electrodes using ActiCHamp (BrainProducts GmbH, Gilching, Germany) will be prepared, followed by registration of the MRI-based TMS-navigator. In both conditions MRI-navigated TMS with 600 pulses per session will be applied to the prefrontal cortex. The intervention protocol (EEG-synchronized rTMS over left DMPFC or standard iTBS over left DLPFC) depends on the randomization. The patients will not be informed about their assignment to the experimental or control protocol.

At the start of each study visit, patients will be asked about changes in medication. The patient is asked about the occurrence of any adverse events at the end of each therapy visit and again at each subsequent study visit to account for adverse events that may have occurred between sessions. In the case of adverse events, any event will be documented in the case report form, a study physician will be consulted and feedback is given to the principal investigator and the sponsor. The principal investigator decides on the severity of the adverse event and further study participation in consultation with the patient. In case of changes in the medication, the patient must be excluded from further participation.

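### The medication-stability windows and the consequences of a change conflict between sections, and it is unstated whether MADRS is still rated after an exclusion for a medication change

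*Protocol article*

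**What the plan says.** **Before treatment.** Under *Eligibility criteria*, a patient on an antidepressant qualifies if "it has to be taken for at least 2 weeks before inclusion in the study", with drug and dose unaltered. Under *Relevant concomitant care permitted or prohibited during the trial*, medication at or above the minimum oral dose of the treatment-history form "has to remain unchanged 4 weeks before and 6 weeks during study treatment".

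**On study.** *Eligibility criteria* requires that "no change in medication will be made until the end of the study (last visit takes place 4 weeks after the last therapy session"). *Participant timeline* states: "The TMS intervention duration for each subject is 4 weeks (20 sessions, 5 sessions per week").

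**Consequence of a change.** *Eligibility criteria* says, in both the inclusion and the exclusion list: "If a change in medication is necessary, further study participation is not possible". *Therapy visit* says: "In case of changes in the medication, the patient must be excluded from further participation". Neither section names a dose threshold. *Relevant concomitant care* regards changes below the minimum oral dose as unimportant, has changes after the end of treatment noted at follow-up, and otherwise states: "Critical changes during the treatment period lead to exclusion from the per protocol analysis".

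**Analysis and follow-up.** *Criteria for discontinuing or modifying allocated interventions* says: "Patients who withdraw from the study will be included in the primary statistical analysis". *Methods and analyses* defines the ITT set as all randomised patients except those who withdraw consent to the analysis of their data. *Provisions for post-trial care* continues planned follow-up for a participant who withdraws early, unless consent to follow-up is also withdrawn. *Methods and analyses* expects values to be missing only because patients refuse, and multiply imputes them.

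**The concern.** Site staff are given incompatible instructions on who is eligible, which medication changes matter, and what happens after one. Recruitment is under way, so patients in the same situation may already be handled differently.

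Three parts of the analysis depend on the answer:

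- **The primary endpoint.** Medication is plausibly changed most often in patients who are doing badly. If a change ends participation and with it the ratings, the post-treatment MADRS is missing for a reason related to outcome, and the ITT analysis uses an imputed value where an observed one could have been had.
- **The first-listed secondary endpoint**, MADRS change 4 weeks after the last session. A medication change during follow-up ends participation under one section and is merely recorded under another.
- **The per-protocol analysis.** It is produced only if the ITT and per-protocol sets differ by more than four patients. What counts as a relevant change therefore helps decide whether it is produced at all.

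**Working it through.** **1. Periods in the protocol**

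Inputs: 20 sessions at 5 per week (*Participant timeline*); last visit 4 weeks after the last session (*Eligibility criteria*); up to 4 missed sessions made up at the end (*Criteria for discontinuing or modifying allocated interventions*).

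- Treatment: 20 / 5 = 4 weeks, which reproduces the stated duration.
- Treatment with four make-up sessions: (20 + 4) / 5 = 4.8 weeks.
- Baseline to last visit: 4 + 4 = 8 weeks, or 4.8 + 4 = 8.8 weeks with make-up sessions.

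The 6-week window in *Relevant concomitant care* is longer than treatment (4 to 4.8 weeks) and shorter than the time to the last visit (8 to 8.8 weeks). It corresponds to neither.

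**2. Window before treatment**

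The two rules count from different points: at least 2 weeks before inclusion, and 4 weeks before study treatment. A patient with 2 weeks of stability at inclusion meets both only if at least 4 − 2 = 2 further weeks pass before the first session. No minimum interval is set. The second screening visit, at which inclusion criteria are rechecked, falls within 3 days of the first session. If inclusion is dated from that visit (an assumption, since the article does not date it), a patient who just meets *Eligibility criteria* has at most 14 + 3 = 17 days of stability at the first session, against the 28 days asked for elsewhere. Both rules can be met together, but meeting the first does not guarantee the second.

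**3. Consequence of a change, case by case**

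| Change | *Eligibility criteria* | *Therapy visit* | *Relevant concomitant care* |
|---|---|---|---|
| Below the minimum oral dose, during treatment | participation ends | participation ends | no consequence |
| Critical change, during treatment | participation ends | participation ends | out of the per-protocol analysis |
| After the last session, before the last visit | participation ends | participation ends (question asked at every study visit) | recorded only |

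Read literally, no row has one answer.

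**4. Outcome collection after a change**

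- The analysis set is clear: such patients remain in the ITT set.
- Rating after early withdrawal is covered, but that provision is worded for a participant who withdraws.
- *Therapy visit* describes a patient whom the study excludes. No section says whether that patient is still rated after the final session and at follow-up.
- If not, the values are missing because of a study rule rather than refusal, which the missing-data paragraph does not anticipate.

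**5. Size**

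The article gives no frequency of medication changes, so nothing in it allows the amount of lost data or any bias to be calculated. The sample-size figures are not affected.

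**The case against.** The strongest reply is that the protocol already separates leaving the study from leaving the analysis. The section on discontinuation removes patients for intolerance or missed sessions and, in the same paragraph, keeps those who withdraw in the primary analysis. The ITT definition agrees, and follow-up after early withdrawal is promised. A reader might infer that the exclusion rule deletes outcome data which the ITT analysis needs. The documents do not support this: no section removes such patients or their data. What stands is narrower: it is not said that the follow-up promise applies to a patient excluded for a medication change. The full protocol may settle this, but the article's own sections still conflict.

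Two of the conflicts can be softened. The pre-treatment windows have different starting points. The minimum-oral-dose wording could be read as defining what a change means throughout, although the other sections do not refer to it. Neither reading explains the 6 weeks or the two rules for changes during follow-up.

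A reader might also put a figure on the bias. Suppose 34 randomised (17 per arm), two patients in an arm with a true 10% reduction, each imputed at the planning mean of that arm (48% control, 68% experimental):

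- control arm only: 2/17 × (48 − 10) = 4.5 points, understating the difference;
- experimental arm only: 2/17 × (68 − 10) = 6.8 points, overstating it;
- both arms: 2/17 × (58 − 38) = 2.4 points, overstating it.

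The number of patients, the 10% and the imputed values are all assumed, and even the sign depends on where the cases fall. The plan also has safeguards: percentage of sessions attended as an imputation covariate, a MADRS rating after session 10, and zero-change and last-observation-carried-forward sensitivity analyses. These figures are therefore no estimate for this trial.

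**Conclusion.** The point holds as an internal inconsistency with one open question about data collection. The 6-week window fits no period in the protocol. The pre-treatment windows differ, so that a patient can satisfy one section and fail the other. The same medication change can lead to no action, a note, exclusion from the per-protocol analysis, or the end of participation, depending on the section followed.

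The effect on the primary analysis is conditional. It arises only if exclusion for a medication change is taken to end MADRS rating, and it biases the result only if such changes are related to response, which is plausible but not documented. Its size cannot be stated. Correction is nevertheless worthwhile, because the sections conflict whatever the bias and recruitment continues. Which window or clinical rule is appropriate is not judged here.

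**What to change.** Amend *Eligibility criteria* (both lists), *Relevant concomitant care* and *Therapy visit* so that they share one pre-treatment window with a stated starting point, one on-study window tied to a named visit, one definition of a relevant change, and one consequence. The clinical content of each is for the investigator to decide.

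State as well that the follow-up provision under *Provisions for post-trial care* applies after a medication change: MADRS after the final session and at follow-up is collected in every randomised patient who has not withdrawn consent, and these values enter the ITT analysis. A medication change would then bear on continued treatment or on membership of the per-protocol set, not on whether outcomes are measured. This also brings practice into line with the expectation that values are missing only through refusal.

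The cost is amendment wording and a few ratings at visits already scheduled. Sample size and analysis method are unchanged.
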